## Abstract

**Background:**

Major depressive disorder is among the most burdening and costly chronic health hazards. Since its prognosis is poor and treatment effectiveness is moderate at best, prevention would be the strategy of first choice. Insomnia may be the best modifiable risk factor. Insomnia is highly prevalent (4–10%) and meta-analysis estimates ±13% of people with insomnia to develop depression within a year. Among people with insomnia, recent work identified three subtypes with a particularly high lifetime risk of depression. The current randomized controlled trial (RCT) evaluates the effects of internet-guided Cognitive Behavioral Therapy for Insomnia (CBT-I), Chronobiological Therapy (CT), and their combination on insomnia and the development of depressive symptoms.

**Methods:**

We aim to include 120 participants with Insomnia Disorder (ID) of one of the three subtypes that are more prone to develop depression. In a two by two factorial repeated measures design, participants will be randomized to CBT-I, CT, CBT-I + CT or treatment as usual, and followed up for one year. The primary outcome is the change, relative to baseline, of the severity of depressive symptoms integrated over four follow-ups spanning one year. Secondary outcome measures include a diagnosis of major depressive disorder, insomnia severity, sleep diaries, actigraphy, cost-effectiveness, and brain structure and function.

**Discussion:**

Pre-selection of three high-risk insomnia subtypes allows for a sensitive assessment of the possibility to prevent the development and worsening of depressive symptoms through interventions targeting insomnia.

**Trial registration:**

Netherlands Trial Register (NL7359). Registered on 19 October 2018.

## Background

Major depressive disorder is among the most burdening and costly chronic health hazards. Its prognosis is poor and treatment effectiveness is at best moderate [1]. The Global Consortium for Depression Prevention concluded that our best chance to combat the global burden of depression is to provide preventive intervention to people at risk [2]. Insomnia plays an important role in developing and maintaining depressive symptoms [3] and may be the best modifiable risk factor of depression [4–7]. It has recently been revealed that insomnia comes in five different stable subtypes, of which three have an increased risk of lifetime depression [8]. The current randomized controlled trial (RCT) therefore evaluates the effects of internet-guided Cognitive Behavioral Therapy for Insomnia (CBT-I), Chronobiological Therapy (CT), and their combination on insomnia and the development of depressive symptoms in people with the type of Insomnia Disorder (ID) that are most prone to develop depression.

With a prevalence of 4–10% in the general population, ID is the second most prevalent mental disorder [9]. ID increases the use of health care facilities and contributes to cognitive and health problems including the risk of developing obesity, diabetes, cardiovascular disease and most markedly, of depression [10]. Meta-analysis estimates that 13% of people with ID will develop depression within a year [5]. Not all people with ID are equally likely to develop depression. It has recently been discovered that ID is not a uniform disorder. Rather, people with ID represent a heterogeneous mix of at least five different subtypes, of which three are more prone to developing depression [8]. It is unknown which environmental, psychological, or biological markers of vulnerability underlie the subtypes of ID that are prone to develop depression. Identifying these markers could significantly contribute to our understanding of why some people suffering from ID are vulnerable to developing a depression, while others are resilient.

The most common approach for the treatment of ID is pharmacological therapy [11]. However, pharmacological treatments have a high prevalence of negative side effects, such as daytime drowsiness, risk of abuse or addiction, or relapse of insomnia after withdrawal. More recently developed treatments, and most notably CBT-I, have shown more sustained positive effects, as indicated by increased sleep efficiency and reduced severity of insomnia complaints [12–14]. Internet-based CBT-I has similar positive effects [15–18]. CBT-I consists of both cognitive (e.g., rumination and worrying) and behavioral (e.g., sleep hygiene, stimulus control, and sleep restriction) components [6]. It aims to change a person’s convictions and beliefs about sleep, and to provide behavioral tools for a better management of sleep [19]. Although CBT-I has proven to be effective in reducing insomnia complaints, it is estimated that only about 60% of the treated people show a clinically significant response among whom only about 40% fully remit [12]. In responders, 50–70% of the complaints may not disappear [20]. Meta-analysis indicates that it is not common for CBT-I to increase sleep efficiency to values well above 85% [17], which is commonly considered as the cutoff for a normal sleep efficiency. Thus, in spite of the undisputed effectiveness of CBT-I, there is ample room for further improvement.

A class of treatments that may help improve effectivity are chronobiological treatments, which aim to support the biological clock of the brain, an essential part of sleep regulation [21]. Circadian rhythms, i.e. the 24-h cycles of physiology and behavior, are entrained by ‘Zeitgebers’, which can be both internal and external stimuli, including light, temperature, and physical activity [22]. CT aims to boost the timed occurrence of these ‘Zeitgebers’. Light therapy and physical activity have shown moderately positive effects on sleep parameters in people with ID [23, 24]. Well-timed body warming, by mild physical activity or taking a hot bath, can support the 24-h rhythm in core body temperature. Body warming can improve sleep quality [25]. CT is of interest as well for the aim of preventing depression in people with insomnia as well, because one of the proposed contributions of insomnia to depression is that poor sleep may lead to circadian dysregulation, which predisposes to depression [3].

The theoretical mechanisms underlying CBT-I and CT can be viewed within the two-process model of sleep regulation proposed by Borbely et al. (1982) [26], which proposes that sleep pressure concerns a homeostatic and a circadian process (commonly denoted, respectively as process S and C). During CBT-I the homeostatic sleep pressure is build up via sleep restriction, while imposed adherence to fixed bedtimes is presumed to support the circadian rhythm [27]. CT aims to further entrain and strengthen the circadian rhythm by increasing its amplitude by means of scheduled light exposure, physical activity and body warming [27]. Indeed, both CBT-I and CTs have proven effective to reduce depressive symptoms. A large RCT in insomnia patients found that internet-based CBT-I ameliorated subclinical depression symptoms [28]. Other studies have shown similar results confirming that CBT-I is effective in reducing both insomnia and depressive symptoms [29, 30] and can even prevent a depressive episode at 1 year follow up [31]. Interestingly, a study comparing CBT for insomnia and CBT for depression in comorbid insomnia and depression patients, found that CBT for insomnia was equally effective in reducing depression severity compared with CBT for depression, while more effective in reducing insomnia complaints [32, 33]. Light therapy, probably the strongest of the different CTs, has also demonstrated to ameliorate depressive symptoms not only in patients suffering from seasonal affective disorder, but also in patients with non-seasonal depression [34].

The recent finding that insomnia comes in different subtypes [8] could propel the development of individualized treatment: what is effective for one subtype may not be effective for another subtype. For the three insomnia subtypes that are most prone to develop depression, it is highly relevant to evaluate whether CBT-I or CT interventions aimed at sleep improvement could also prevent worsening of depressive symptoms or the onset of a major depressive episode.

### Objectives

The current RCT primarily aims to evaluate the efficacy of internet-guided CBT-I, CT, and their combination on the development of depressive symptoms during the year following intervention in people with insomnia of the subtypes that have a high risk of developing depression. The RCT will also evaluate how the treatments affect insomnia symptoms during the year following intervention, and explore how the interventions affect brain structure and function as assessed with Magnetic Resonance Imaging (MRI).

The RCT is embedded in a more extensive study aimed at a better understanding of causes and consequences of insomnia. Extensive data will be assessed to explore multivariate predictors of the development of depression and insomnia, as well as treatment responses, in the year following intervention. Moreover, the same extensive data will be assessed in controls without sleep complaints and people with insomnia of the subtypes that do not have an increased risk of developing depression. This will allow us to explore multivariate differences across controls and insomnia subtypes. The current manuscript focuses on the RCT within this extensive study.

## Methods/design

### Research design

The study is a parallel-group repeated measures RCT examining the efficacy of CBT-I, CT, and their combination, versus treatment as usual. At baseline (T0), participants of the subtypes with increased risk of developing depression are assessed for baseline values, and randomized to one of the four intervention groups, and will be followed up after completion of the intervention at T1 (week 7), and subsequently at T2 (week 26), T3 (week 39) and T4 (week 52). Figure 1 shows a flow chart of the research design. The study was approved by the Medical Ethics Committee of the VU University Medical Centre (NL63139.029.17). Participants are included only after their written informed consent. The trial is registered with the Netherlands Trial Register (NL7359).

**Fig. 1 Fig1:**
[figure not shown]
Flowchart diagram showing a summary of the study design. DSM-5: Diagnostic and Statistical Manual of Mental Disorders, 5th edition; ISI: Insomnia Severity Index. CIDI: Composite International Diagnostic Interview; CBT-I: Cognitive Behavioral Therapy for Insomnia; CT: Chronobiological Therapy; TAU: treatment as usual

### Participants

The RCT aims to include 120 people with ID of the subtypes with increased risk of developing depression. Inclusion criteria are: 1) meeting the criteria of ID according to the Diagnostic and Statistical Manual of Mental Disorders, 5th edition (DMS-5) [35], and the International Classification of Sleep Disorders, 3rd edition (ICSD-3) [36]; 2) an Insomnia Severity Index score (ISI) ≥ 10 [37]; 3) classification as insomnia type 1, 2, or 3 according to the Insomnia Type Questionnaire [8]; and 4) age between 18 and 70 years. Exclusion criteria are: a) current major depressive disorder according to self-report, a clinical diagnosis, or the Composite International Diagnostic Interview Short Form (CIDI-SF) [38]; b) current treatment with antidepressant medication; c) current CBT-I treatment; d) a diagnosis of or probable severe obstructive sleep apnea syndrome (Apnea Hypopnea Index ≥15 [39], or high risk according to the Berlin questionnaire [40]), moderate to severe restless legs syndrome (International Restless Legs Scale > 15 [41]), or severe periodic limb movement disorder (Periodic Limb Movement Index ≥ 25); e) a self-reported diagnosis of a severe neurological or psychiatric disorder; f) self-reported severe physical or mental impairment due to stroke, or traumatic head injury; g) night work or rotating shift-work; h) a known eye condition incompatible with light exposure; i) a history of light-induced migraine or epilepsy, or severe side effects to bright light in the past; or j) MRI contraindications such as non-MR compatible metal implants, claustrophobia, or pregnancy. The use of sleep medication is allowed and monitored. Participants will be recruited among the participants of the Netherlands Sleep Registry (www.sleepregistry.org), through media advertisements, and through flyers. It will be documented whether participants were recruited from the sleep registry or via media advertisements and flyers.

### Randomization

Participants of the RCT will be randomized to one of the four groups: CBT-I, CT, combination of CBT-I and CT, and treatment as usual (*N* = 30 for each group). Simple randomization will be applied until 2 to 4 participants have been randomized to each of the four groups. In order to ascertain balanced and equally sized groups across the intervention conditions, subsequent participants will be assigned according to covariate adaptive randomization [42]. Matching variables include age, sex, insomnia type, baseline severity of insomnia (ISI [37]) and depressive symptoms (Inventory of Depressive Symptoms – Self Report, IDS-SR [43]), use of sleep medication, suspected mild sleep disordered breathing, suspected mild restless leg syndrome, Body Mass Index (BMI), time of year at inclusion, and group size at inclusion. Since matching includes both continuous and categorical covariates, randomization will be done following the method proposed by Frane [44]. This method evaluates between-group differences for each of the covariates in case a new participant would be assigned to each of the treatment groups by obtaining *P* values from analysis of variance (ANOVA) for the continuous covariates and Chi-square tests for the categorical covariates. For each covariate, this procedure provides four *P* values, one for each possible group assignment. This smallest of all P values identifies the least desirable assignment. Of the four possible group assignments, the most desirable will be the one that maximizes the smallest *P* value across all covariates. This will be the final group assignment for that participant, because it keeps imbalance over groups as small as possible. The randomization is performed using R [45].

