### Statistical analyses

Statistical analyses aim at determining the relative efficacy of internet-guided CBT-I, CT treatments and their combination, for the prevention of worsening of depressive symptoms in people with the type of ID that heralds increased risk of developing depression. The long-term effects of interventions and their interactions on depressive symptoms and on the probability to develop a diagnosis of depression will be estimated with mixed effect linear and logistic regression models using R [45].

In order to allow for an intention-to-treat analysis including all available data while accounting for a possibly variable number of missing data, hierarchical mixed effect linear and logistic regression models will be employed. Regressors are a random intercept, time, dummy-coded assignment to CBT (yes = 1, no = 0) and CT (yes = 1, no = 0) and a dummy coded variable indicating follow-up (T1-T4 = 1) versus baseline (T0 = 0). The interaction effect estimates of interest are CBT by follow-up, CT by follow-up and CBT-I by CT by follow-up [64]. The time variable estimates linear changes over time. Ancillary analyses will evaluate treatment by time effects (i.e., treatment effects changing linearly over time). Linear mixed effect models will also be used evaluate secondary outcomes (insomnia severity, cost-effectiveness, brain function and structure). A logistic mixed effect model will be used to evaluate the secondary outcome of a diagnosis of depression at T4. We will explore the effect of various variables, including the number of previous depressive episodes, time since last depressive episode, and expectation of intervention effectiveness.

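### Depression history is not matched on and is left to exploration, although past depression is no exclusion; the effect is modest for IDS-SR and matters more for the T4 diagnosis

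*Protocol article*

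**What the plan says.** **Selection.** The Background states that "insomnia comes in five different stable subtypes, of which three have an increased risk of lifetime depression", and the abstract speaks of "recent work identified three subtypes with a particularly high lifetime risk of depression". Inclusion criterion 3 (Participants) admits only those three types.

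**Exclusions.** Exclusion a) removes current major depressive disorder. Two others also bear on depression: "current treatment with antidepressant medication" and "a self-reported diagnosis of a severe neurological or psychiatric disorder". None names a past depressive episode.

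**Allocation.** The Randomization section begins its list with "Matching variables include age, sex, insomnia type, baseline severity of insomnia (ISI [37]) and depressive symptoms" and continues with "use of sleep medication, suspected mild sleep disordered breathing, suspected mild restless leg syndrome, Body Mass Index (BMI), time of year at inclusion". The last item is the current size of each arm. That makes ten characteristics at inclusion plus arm size. Depression history is not among them.

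**Analysis.** The Statistical analyses section lists the regressors of the mixed model: random intercept, time, the two treatment dummies and a follow-up dummy. The estimates of interest are the treatment-by-follow-up interactions. History comes in afterwards: "We will explore the effect of various variables, including the number of previous depressive episodes, time since last depressive episode".

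**Outcomes.** The primary outcome is IDS-SR over T1 to T4 relative to baseline. A CIDI-SF diagnosis of major depressive disorder at T4 is secondary.

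**The concern.** The subtypes were chosen for a depression risk expressed over the lifetime, so a good share of entrants may already have had an episode. An unmedicated person in remission can enter beside someone who was never depressed. A previous episode is a plausible predictor of the course over the following year. The sponsor evidently thinks so too, since the number of episodes and the time since the last one are named for exploration. Yet the allocation balances BMI and suspected mild restless legs, and neither the allocation nor the main model takes account of previous depression.

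Two things are at stake. First, a chance difference in history between the levels of a treatment factor could shift the estimates. Second, a T4 diagnosis may be a first onset in one participant and a recurrence in another, and no split of the two is planned. Both lists are given explicitly in the article, so this is a choice it makes and not a detail it leaves open.

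**Working it through.** **1. The plan's own figure.** Inputs from Sample size calculation: alpha 0.05 (taken as two-sided), power 0.80, ICC 0.50, 26 completers per group, hence 52 v 52 for a main effect.
- Variance of the mean of four follow-ups minus baseline: (1 - 0.5) x (1 + 1/4) = 0.625 in SD² units.
- Detectable main effect: (1.960 + 0.842) x sqrt(0.625 x 2/52) = 0.434.
- The stated 0.44 reproduces and is used as the yardstick.

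**2. How large an imbalance in history could be.** The article gives no prevalence of past depression, so q = 30-60% is assumed. Allocation is taken as independent of history, with 60 v 60.
- SD of the difference = sqrt(2q(1 - q)/60).
- q = 0.3: sqrt(0.42/60) = 0.084. q = 0.5: sqrt(0.50/60) = 0.091. q = 0.6: sqrt(0.48/60) = 0.089.
- Exact binomial probability of a difference of at least 15 points: 9% to 12% over this range. At least 20 points: 2% to 4%.

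**3. What it does to the IDS-SR main effect.** Only an effect of history on change from baseline matters. Assume 0.2-0.5 SD.
- 0.15 x 0.2 = 0.03 SD and 0.15 x 0.5 = 0.075 SD.
- Relative to 0.44: 0.03/0.44 = 7% and 0.075/0.44 = 17%.

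**4. Which model term would help.** The treatment-by-follow-up estimate is a within-person contrast, so a term that is constant over time drops out when data are complete. One simulated complete data set (120 people, random-intercept model, 28-point imbalance in history) shows this for the CBT-by-follow-up estimate:

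| Model | Estimate |
|---|---|
| Without history | 0.0779 |
| History as main effect | 0.0779 |
| History-by-follow-up added | 0.0341 |

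Only the interaction term adjusts the primary estimate.

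**5. Effect of that term on precision.** If history explains g²q(1 - q) of the 0.625, with g = 0.2-0.5 and q = 0.3-0.5:
- Smallest gain: 0.625 - 0.04 x 0.21 = 0.6166, detectable effect 0.431.
- Largest gain: 0.625 - 0.25 x 0.25 = 0.5625, detectable effect 0.412.
- N = 120 does not change.

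**6. The T4 diagnosis.** Exclusion a) means nobody has the diagnosis at T0, so baseline diagnosis carries no prognostic information. Expected cases at the Background's 13% per year: 0.13 x 120 = 15.6, about 16, or about 4 per arm. With history assumed at 50% and equal risk, that is about 2 per arm for first onset and 2 for recurrence. The 13% refers to insomnia in general. The article gives no rate for these subtypes and no relative risk by history, so the shift in this outcome is not quantified here.

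**The case against.** The best defence is that the main prognostic information is already handled. The characteristic on which people are selected, insomnia type, is matched, and so is baseline IDS-SR. The primary estimate is change from baseline, which removes any constant effect of history on symptom level. Chance imbalance is part of the standard error and is not bias. Which factors to match beyond ten is a design preference, and the article contradicts and miscalculates nothing here. For IDS-SR most of this stands, and it is why the effect is modest. One qualification is that, after the first 2 to 4 participants per group, the described rule picks the best-balanced assignment with no stated random element. The usual appeal to randomisation for unmatched factors is therefore somewhat weaker than under simple randomisation.

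The defence is weaker for the T4 diagnosis. All three types are high-risk and each can contain people with and without past episodes. IDS-SR measures current symptoms, not past episodes.

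Some stronger readings are tempting but not supported:
- *That only a current episode is excluded.* Current antidepressant treatment and self-reported severe psychiatric disorder are excluded too, which removes some remitted or treated people.
- *That history is ignored.* It is planned for exploration. What is missing is a pre-specified place in the main model.
- *That the prevention conclusion cannot be read.* The abstract and Discussion speak of preventing the development and worsening of depressive *symptoms*. A change in IDS-SR is readable without separating first onset from recurrence. Only the secondary diagnosis is touched.
- *That a shift of 0.09 SD, a fifth of the detectable effect, is to be expected.* That figure takes the 95% limit of imbalance at 50% prevalence (1.96 x 0.091 = 0.18) and multiplies it by the top assumed shift of 0.5 SD. It is an upper-end case, and it ignores any correlation of history with the matched factors.

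**Conclusion.** The point holds as a specific, inexpensive improvement, not as an error in the plan. Past depression is not excluded, is not in the matching list and is not in the main-model regressors, in a sample chosen for lifetime depression risk.

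For IDS-SR the likely consequence is small: 0.03-0.075 SD at a 15-point imbalance, which has a chance of about 9-12% if allocation is unrelated to history. This rests on an assumed 30-60% prevalence and an assumed 0.2-0.5 SD shift in change from baseline. Neither figure is in the article.

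The stronger case is the diagnosis at T4. There the baseline diagnosis does not vary, history is the natural prognostic factor, and first onset and recurrence would otherwise be pooled. A reader might infer that the trial should therefore test the two separately. At about 16 expected cases it cannot, so the split is useful only as description.

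**What to change.** 1. **Allocation.** Add previous major depressive episode (none / one or more) to the matching variables for participants still to be enrolled. Trial status dates the start of data collection to December 2018, so some participants may already be allocated.
2. **IDS-SR model.** Pre-specify a history-by-follow-up term together with its main effect. A main effect alone leaves the treatment-by-follow-up estimate unchanged in complete data.
3. **Diagnosis model.** Pre-specify the same binary history variable as a covariate.
4. **Reporting.** Tabulate T4 diagnoses by arm as first onset or recurrence, descriptively and without tests.

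If the allocation can no longer be changed, items 2 to 4 still apply.

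**Cost.** One more binary covariate in the R allocation script, with slightly less tight balance on the other factors, and one or two extra model terms. The planned exploration implies that history is recorded, but it must be available before allocation. With few events, even one added covariate is a noticeable load on the diagnosis model, so history should stay binary there. The sample size is unaffected.

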### Blinding

Participants of the RCT will be informed of their intervention condition after all baseline assessments at T0 are completed. The research team will be blind to treatment allocation during the baseline assessments at T0. The team member who runs the R script that allocates participants to one of the treatment groups, will not be blinded to the intervention conditions, but is unaware of therapy conditions when communicating with the participants. The CIDI interviewers will be blind to intervention conditions and will be independent from the therapy coaches. During treatment, therapy coaches will not be blind to the intervention conditions, since they have to provide the participants with feedback on the therapy sessions. During data analyses, all data will be coded regarding intervention condition and analysts will not have access to the key document. Only after statistical analyses are completed, conditions may be revealed.

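### After the burn-in the allocation rule has no chance element, and the script is run by an unblinded team member with participant contact whose stated unawareness has no mechanism

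*Protocol article*

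**What the plan says.** The Randomization section of the protocol article describes two stages. First: "Simple randomization will be applied until 2 to 4 participants have been randomized to each of the four groups". Then "subsequent participants will be assigned according to covariate adaptive randomization", using eleven matching variables: age, sex, insomnia type, ISI, IDS-SR, sleep medication, suspected mild sleep-disordered breathing, suspected mild restless legs, BMI, and finally "time of year at inclusion, and group size at inclusion". For each candidate arm the script computes one P value per covariate. "Of the four possible group assignments, the most desirable will be the one that maximizes the smallest" P value, and "This will be the final group assignment for that participant, because it keeps imbalance over groups as small as possible". No biased coin, other random step or tie rule appears in this description.

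The Blinding section covers who does this. For the baseline period it states: "The research team will be blind to treatment allocation during the baseline assessments at T0". One person is treated separately: "The team member who runs the R script that allocates participants to one of the treatment groups" is said to be someone who "will not be blinded to the intervention conditions, but is unaware of therapy conditions when communicating with the participants". Participants learn their condition once all T0 assessments are done.

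**The concern.** The rule is set out step by step and ends in a definite assignment, so this is a stated property of the method and not a detail left to a fuller document. Given the accrued list and the new person's covariates, the arm is known with certainty.

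The person placed to know it is an unblinded team member who also talks to participants. Several inputs leave room for influence. Two are rated as suspected conditions. Time of year and group size depend on when a person is entered. Eligibility can also still be open during T0: Table 1 places the CIDI-SF and MRI at baseline, and current depression and MRI contraindications are exclusions.

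The stakes come from the primary outcome. The IDS-SR is self-reported, participants know their condition, and the comparator is treatment as usual without either online module. Blinding therefore does not protect the primary endpoint, which leaves concealment at entry as one of the main protections against selection.

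**Working it through.** **Inputs.** Four arms, 120 participants, 30 per arm, burn-in target m = 2 to 4 per arm, then the max-min-P rule (Participants and Randomization sections). The article gives no figure for the rule-assigned share, so there is none to reproduce.

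**Minimum burn-in.** 4 × 2 = 8 to 4 × 4 = 16. That leaves 120 − 16 = 104 to 120 − 8 = 112 people, or 104/120 = 87% to 112/120 = 93%.

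**Expected burn-in.** Simple randomization does not fill arms evenly. With equal probabilities, the chance of stopping at exactly the minimum is (4m)! / [(m!)^4 × 4^(4m)].
- m = 2: 2,520 / 65,536 = 3.8%.
- m = 4: 63,063,000 / 4,294,967,296 = 1.5%.

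If every arm must reach m, 40,000 simulated burn-ins give:

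| m per arm | Mean length | 5th to 95th percentile | Left for the rule, on average |
|---|---|---|---|
| 2 | 14.2 | 9 to 23 | 105.8 of 120 = 88% |
| 4 | 24.7 | 18 to 36 | 95.3 of 120 = 79% |

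**How deterministic the rule is.** It was run on 24 simulated 120-person trials, with assumed distributions for five continuous and five categorical covariates plus group size. It named a unique arm for about 97 to 98% of rule-assigned participants. The other 2 to 3% were exact ties.

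**Who can compute it.** The chosen arm was among the currently smallest in only about 32% of rule-based assignments, so arm counts alone do not reveal it. The script, the running list and all the person's covariates are needed. Table 1 shows the IDS-SR first at T0, after consent at enrolment. The exact arm can therefore be computed only after consent, but it can be computed before T0 is complete.

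**Cost of adding chance.** Under the same kind of assumed covariates, giving the preferred arm probability 0.8 (the others 0.2/3 = 0.067 each) had these effects:
- The largest between-arm difference in means, averaged over runs, rose from about 0.15 to 0.21 SD. Under simple randomization it was about 0.40 SD.
- The gap between the largest and smallest arm rose from about 5 to about 7 people.
- The baseline-adjusted standard error of a main effect barely moved (0.112 against 0.113).

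**The case against.** Much can fairly be said on the other side.

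- **Size.** Treating 8 to 16 as the actual burn-in gives 87 to 93% rule-assigned. Those are minimum burn-ins, and the average share is lower. This stands, and the figure used here is roughly 80 to 88%.
- **Known in advance.** A reader might infer that staff in general can foresee the next assignment, or that candidates can be screened by arm before consent. The documents do not support this. Exposure is limited to whoever holds the script, list and T0 covariates, between data entry and assignment.
- **Certainty against one in four.** Comparing certainty here with a one-in-four guess under simple randomization is not like for like, because the holder of a pre-generated list would also know the arm. A 0.8 rule still leaves the script holder right about 80% of the time. So who runs the script, and when, matters at least as much as the coin.
- **The Blinding sentence.** It is tempting to call it a flat contradiction. It limits the unawareness to contact with participants, so separation in time or by coding could reconcile it. The Research design section also mentions baseline assessment before randomization. What remains is that no mechanism is given, and that the Blinding section dates when participants are informed but not when the script is run.
- **Cost.** The low cost in precision assumes covariate adjustment, and the model in the Statistical analyses section lists no allocation covariates. Recruitment has begun, so the change would give one trial two allocation rules. Both points stand and are carried into the fix.

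None of this supplies a chance element to the rule or explains how the allocator stays unaware.

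**Conclusion.** The point holds as a cheap improvement worth making. As written, roughly 80 to 88% of the sample on average is assigned with probability 1, rare ties aside, by a script run by an unblinded team member with participant contact. The share assumes equal-probability simple randomization until every arm reaches 2 to 4. The tie rate and the cost of the remedy rest on assumed covariate distributions, because the article gives none.

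A reader might go further and infer that selection has occurred or that the trial's comparison is biased. The documents show an opening for selection, not its use. The sample-size and power figures are unaffected, because they rest on arm sizes, dropout and the ICC, not on how the arms were filled.

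**What to change.** For participants still to be allocated:

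1. Assign the preferred arm with probability of about 0.8 and share the rest equally among the other three. Log the seed and break ties at random.
2. Run the script once per participant, only after eligibility is confirmed and the T0 covariates are locked.
3. Give the task to an existing team member without participant contact.
4. Reconcile the sentence in the Blinding section by stating what the allocator knows, when, and what keeps the arm hidden during contact.
5. Add the allocation covariates to the model in the Statistical analyses section. Baseline IDS-SR already enters as the T0 response, and group size is not a patient characteristic. The others should also enter by their interaction with the follow-up indicator, because the treatment effect is estimated as a change from baseline.

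Report the participants already allocated as assigned by deterministic minimisation after a simple-randomization burn-in, and give the date of the change. If recruitment has closed, only the clarification, the adjustment and the reporting apply.

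The cost is a short script change, a reassigned task and a documented mid-trial change of rule, with slightly larger covariate imbalance (about 0.15 to 0.21 SD for the largest between-arm difference).
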